### Methods for additional analyses (e.g., subgroup analyses) {20b}

When possible (i.e., enough patients are available), the analyses will be performed stratified by center.

### Methods in analysis to handle protocol non-adherence and any statistical methods to handle missing data {20c}

Protocol non-adherence will be handled by performing the analyses according to the ITT principle, specifically, patients will be analyzed considering their allocation group regardless of the intervention they will follow. Moreover, deviation from the protocol will be registered as well as the reason for deviation. The missing rate is expected to be very low, therefore no specific analyses to handle missing data are planned. However, if needed (i.e., missing rate between 20 and 40%) multiple imputation through expectation–maximization algorithm will be applied and the results obtained from analysis of the new data will be considered as sensitivity analysis.

### Plans to give access to the full protocol, participant-level data, and statistical code {31c}

Public access to the full protocol and statistical methods will be obtained by publishing the study protocol in an open-access journal. Study protocol has been submitted to ClinicalTrials.gov (identifier: NCT05513508).

### Composition of the data monitoring committee, its role and reporting structure {21a}

The data monitoring group is composed by [name] (lead investigator), [name] (lead investigator), and [name] (lead investigator). The role of the data monitoring committee is to independently review the study protocol, recruitment of patients and liaising with the principal investigator to be involved in the safety monitoring interim analysis, and agreement on the final manuscripts. The Data Quality Assurance group is composed by [name], [name], [name], [name], and [name] and will be responsible for monitoring data for inconsistency and missing data.

### Adverse event reporting and harms {22}

Interfaces for noninvasive ventilation should be considered as a non-significant risk device according to the definition given from the Food and Drug Administration. Besides, the present randomized controlled trial does not intend to investigate a new interface but the protocolized rotational use of commercially available interfaces. As patients with contraindications to NIV/with known hypersensitivity to skin protective devices will be excluded from the study, the potential for serious adverse events related to a protocolized rotation use of interfaces appears remote. Possible minor adverse events consequent to the use of noninvasive ventilation interfaces consist of pressure sores, dryness of the mouth, eye redness, and discomfort. All these information will be recorded and reported as primary and secondary outcomes of the study.

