Stage II	The skin blisters or forms an open sore. The area around the sore may be red and irritated.
Stage III	The skin now develops an open, sunken hole called a crater. The tissue below the skin is damaged. It is possible to see body fat in the crater.
Stage IV	The pressure ulcer has become so deep that there is damage to the muscle and bone, and sometimes to tendons and joints.
Unstageable	Is not possible to see the bottom of the sore, and it is impossible to establish how deep it is
Suspected deep tissue injury	The surface of the skin looks like a Stage 1 or 2 sore, but underneath the surface, it appears as a Stage III or IV.

Discomfort due to the mask will be evaluated every 12 h using a 5-level Likert-like scale [17, 37] to answer the questions “How is your level of discomfort related to the mask?”. The extremes of the scale are “1—no discomfort” and “5—unbearable discomfort,” with three intermediate levels: “light discomfort,” “moderate discomfort,” and “intense discomfort”).

In both groups, in case of the presence of a new pressure ulcer, the strategy that can be applied comprehend (1) application of a wound care dressing or a different kind of wound care dressing; (2) reduction of the time spent on NIV; and (3) change interface.

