### Outcomes {12}

The primary effectiveness outcome is the proportion of patients developing at least one pressure sore of any stage at 36 h from randomization. The reason why this measure of effectiveness was chosen is that it is more clinically relevant than the overall number of pressure sores. Furthermore, 36 h seems to be an appropriate time point given that the time it takes for pressure sores to develop is extremely variable, but it might as well be very short.

Secondary outcomes will be the onset, number, and stage of pressure sores and comfort during NIV measured at different time points (12, 24, 36, 48, 60, 72, 84, 96 h). At the same time points, the location of pressure sores per patient will also be recorded, i.e., forehead, nose bridge, left cheek, right cheek, chin, left periauricular, right periauricular, and occipital. The study will also monitor the number of patients that interrupts NIV due to discomfort, the presence/absence of eye irritation in relation to both oronasal and full face/hybrid mask, poor adherence to the protocol (e.g., duration of NIV treatment/day, interfaces changed and hygiene protocol application both during each 12-h protocol period) and the presence/absence and types of vasoactive medications, i.e., epinephrine, norepinephrine, vasopressin, dobutamine, dopamine, other. Further outcomes include the costs for intervention implementation (e.g., mask-related costs) and those related to the care of pressure sores (antibiotic treatment, specialist medical visits).

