## Data collection and management

### Plans for assessment and collection of outcomes {18a}

A REDCap database will be set up to collect the information needed for the study. The database will consist of ten sheets. The first one will contain the baseline demographic and clinical characteristics of the patients. Eight sheets will store information on primary and secondary outcomes at each time point. The last one will enlist information on patient discharge and the overall treatment. More specifically, the following variables will be recorded:*Baseline characteristics*: age, sex, hospitalization date, nutritional status, body mass index, Braden scale, frailty index, sensorium (Kelly score), Charlson index, chronic steroids therapy, domiciliary NIV or CPAP, NIV treatment goal.*Outcome assessment:* presence and number of pressure sores, location, comfort score (numerical rating scale from 1 to 5), stage for each lesion, fever, humidification, vasoactive medication, NIV interruption, daily NIV duration, hygiene protocol application, eye irritation, interface change, time interface change, NIV ventilator, circuit type, expiratory positive airway pressure, inspiratory positive airway pressure, leaks, medical treatment for the pressure lesions and eventual skin specialist consult.*Discharge:* discharge date, length of hospital stay, discharge status.

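### The harms section says all four named interface harms are reported as outcomes, but dry mouth is in neither the outcome list nor the recorded variables

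*Protocol article*

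**What the plan says.** Adverse event reporting and harms {22} argues that serious harm from rotating marketed interfaces is unlikely. It then lists the minor harms: "Possible minor adverse events consequent to the use of noninvasive ventilation interfaces consist of pressure sores, dryness of the mouth, eye redness, and discomfort". The reporting plan for these is one sentence: "All these information will be recorded and reported as primary and secondary outcomes of the study".

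Outcomes {12} sets the primary outcome: "The primary effectiveness outcome is the proportion of patients developing at least one pressure sore of any stage at 36 h from randomization". It continues: "Secondary outcomes will be the onset, number, and stage of pressure sores and comfort during NIV measured at different time points", at eight times from 12 to 96 h. Among the further monitored items is "the presence/absence of eye irritation in relation to both oronasal and full face/hybrid mask". Dry mouth is not mentioned there, nor among the outcomes in the Abstract.

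Plans for assessment and collection of outcomes {18a} describes eight outcome sheets, one per time point, and names the variables they hold. The list includes the presence, number, location and stage of sores, the comfort score, humidification and, in one run, "hygiene protocol application, eye irritation, interface change, time interface change". It has no entry for dry mouth.

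Relevant concomitant care {11d} mentions mucosal dryness once, as one of two reasons to consider heated humidification.

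**The concern.** The harms section sets up no adverse event collection of its own for these four events. It points to the outcomes and relies on them. Any named harm that is missing from the outcomes and the variable list is therefore missing from the published harms plan.

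At stake is whether the trial can deliver the harms report it promises. If dry mouth is not recorded during the study, the final report will either omit it without comment or have to explain why a harm named in advance has no data. It cannot be recovered from other fields. Humidification is recorded, but it is left to the attending physician, and thick secretions are a second reason for it, so its use does not show whether a patient had a dry mouth.

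**Working it through.** The claim rests on no sample size, power or error-rate figure, so there is no stated number to reproduce. The check takes each harm named in {22} and looks for it first in Outcomes {12} (and the Abstract), then in the variable list in {18a}.

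| Harm named in {22} | Outcomes {12} | Variable list {18a} |
|---|---|---|
| Pressure sores | Yes: primary outcome at 36 h; also secondary (onset, number, stage) | Yes: presence, number, location, stage |
| Discomfort | Yes: secondary outcome (comfort), eight time points | Yes: comfort score, 1 to 5 |
| Eye redness | Yes, as eye irritation, a monitored item tied to both mask groups | Yes, as eye irritation |
| Dry mouth | No | No |

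The count is 3 of 4 harms with both an outcome entry and a variable, and 1 of 4 with neither.

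Two readings could close the gap, and both were checked.

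1. Dry mouth might be covered under another name. The only candidate is the mucosal dryness in {11d}, which is a prompt for care and is neither defined nor recorded as an observation. The humidification variable in {18a} records a treatment, not the symptom.
2. Dry mouth might be part of discomfort. The question put to patients is "How is your level of discomfort related to the mask", answered as one overall level from 1 to 5. It gives no cause, and {22} itself lists dry mouth and discomfort as separate items.

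Neither reading supplies an outcome or a variable for dry mouth.

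**The case against.** The best defence is that a journal article condenses the full protocol and that the case report form is not shown. A dry-mouth field may exist there. This limits the conclusion: it cannot be said that dry mouth will go unrecorded, only that the published plan has no place for it. It does not remove the point. The harms section makes a positive statement about the trial's outcomes, and the outcome list is in the same article. Both lists are also detailed. Outcomes {12} names eight sore locations and five vasoactive drugs, and {18a} goes down to circuit type and leaks.

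A reader might infer more, on two counts.

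- *Eye irritation.* With 6-hourly alternation, a 12 h window in the rotation arm holds 12/6 = 2 mask periods. A reader might conclude that irritation cannot be assigned to a mask on any of the eight sheets. The article does not support this. It nowhere says that a sheet holds a single eye-irritation entry, Outcomes {12} states the intention to relate irritation to both mask groups, and field layout belongs to the case report form. Eye irritation is also recorded, so it does not conflict with the harms sentence.
- *Discomfort.* A reader might conclude that the 12-hourly question always falls at the end of the same mask's turn and so hides discomfort in the rotation arm only. This is not supported either. Control patients can also change mask within a window because of unbearable discomfort. In the rotation arm, a patient who finds one mask unbearable continues on the other, so a later low score correctly describes the mask in use. Planned breaks, weaning and up to 2 h of NIV before randomization shift the mask times against the assessment times. Worst discomfort per patient is not an outcome of this trial.

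Splitting either item by mask on the assessors' form could also reveal alternation to staff who are meant to be blinded.

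**Conclusion.** The point holds for dry mouth alone. The statement in {22} is wrong as written for one of the four harms it names, because neither the outcome list nor the variable list provides for it. Severity is minor: it concerns one minor harm and leaves the primary outcome, its analysis and the sample size untouched.

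The conclusion assumes that the lists in {12} and {18a} reflect what is collected, and that eye redness and eye irritation mean the same thing. If the case report form already has a dry-mouth field, what remains is an omission in the published lists. Nothing here shows that eye irritation or discomfort is inadequately captured.

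**What to change.** Add dry mouth (yes/no) to the existing 12-hourly outcome sheet in {18a} and to the secondary outcomes in {12}, and report it by arm at the same eight time points. One entry per visit, not split by mask, says nothing about which interfaces were worn and so leaves the assessors' blinding as it is. The cost is one extra field on a form already completed at each visit, at most 96/12 = 8 entries per patient.

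If dry mouth will not be collected, reword the sentence in {22} so that it promises only pressure sores, eye irritation and discomfort as reported outcomes. That costs one edited sentence. For patients already enrolled before the field is added, the report should say that dry mouth was not recorded.

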### Frequency and plans for auditing trial conduct {23}

At the start of the trial, the coordinating center will conduct a tutorial on the web-based data entry system. Overall quality and completeness of the data will be checked every six months.

### Plans for communicating important protocol amendments to relevant parties (e.g., trial participants, ethical committees) {25}

Any modifications to the protocol that may impact the conduct of the trial will require a formal amendment to the protocol. All amendments to the protocol must be approved by the internal review board of each participating center. Administrative changes to the protocol, minor corrections, and/or clarifications that have no effect on the way the trial is to be conducted will be agreed upon among the participating centers.

### Dissemination plans {31a}

The ROTA-USE STUDY group will publish the study findings, whatever they are. The main manuscript will be submitted by the writing committee on behalf of the research group. The principal investigators of the three top enrolling centers will be included and engaged in the writing process. Collaborative authorship (i.e., group author under the name of ROTA-STUDY group) will be offered to the principal investigators and research nurses of all the centers including at least 20 patients.

## Discussion

All the issues have been covered in the above sections.

## Trial status

The ROTA-USE protocol, version I (01/07/22), has been approved by the research ethics committee of the coordinator center on the 16/09/22, and recruitment has started in December 2022 at the coordinating center. The remaining centers are undergoing ethics committee evaluation. Recruitment is expected to be completed within September 2024.

## Data Availability

Access to the database will be restricted to the coordinating team, and third parties will only have access to it upon receiving the authorization from the principal investigator, who will analyze each research proposal and statistical analysis plan.

## Abbreviations

ARF: Acute respiratory failure
COPD: Chronic obstructive pulmonary disease
CPAP: Continuous positive airway pressure
CRF: Case report form
PEEP: Positive end-expiratory pressure
ICER: Incremental cost-effectiveness ratio
ICU: Intensive care unit
ITT: Intention-to-treat
mITT: Modified intention-to-treat
NIV: Noninvasive ventilation
PaCO_2_: Arterial partial pressure of carbon dioxide
PaO_2_: Arterial partial pressure of oxygen
PS: Pressure support
RCT: Randomized controlled trial
REB: Research ethics board
